**Abstract**

**Background:** Non-specific mechanical low back pain is highly prevalent, recurrent and is a leading cause of disability worldwide. Despite increased efforts in improving care, the self-reported levels of disability in individuals with LBP have not improved in the last decade. In order to more effectively manage LBP through non-pharmacological approaches, evidence endorses the use of classification systems to support diagnosis and guide treatments. However, this approach to care is not without limitations and a more comprehensive and broader perspective is needed. Hence, we recently proposed and validated the Low Back Pain and Disability Drivers Management (PDDM) model, which aims to identify the domains influencing pain and disability to create an ICF-based profile or phenotype to guide clinical decisions. The objective of this study is to assess the feasibility of conducting a trial and to gather preliminary effect outcomes of the intervention in clinical setting.

**Methods:** The design is a prospective single arm experimental design. Physiotherapists (PTs) working with a population suffering from musculoskeletal disorders and patients presenting with non-specific mechanical LBP from two different clinical settings will be recruited. The intervention consists of a one-day training workshop for PTs on using the PDDM to guide management decisions. PTs will then perform a 6-weeks follow-up with their participating patients. This feasibility study will assess recruitment and retention rates as well as PTs’ acceptability and patients’ satisfaction outcomes related to the intervention. Preliminary effect outcomes will also be gathered.

**Discussion:** This study will inform the feasibility and acceptability of the intervention and gather preliminary outcomes to conduct a future randomised controlled trial to measure the effectiveness of the intervention in managing non-specific mechanical LBP.

**Keywords: Low back pain, Pain management, Rehabilitation, Feasibility outcomes**

**Background**

Non-specific mechanical low back pain (LBP) is defined as “a symptom for which we are currently unable to reliably identify the pathology” [1]. This painful musculoskeletal problem is highly prevalent (up to 84% lifetime prevalence), recurrent [2] and is a leading cause of disability in both high- and low-income countries [3]. Despite increased awareness for health systems and decision makers in improving care, the self-reported levels of disability in individuals with LBP have not improved in the last decade [4]. Managing disability is crucial since it is a strong predictor of chronicity [5] and has important negative social impacts and costs.

Studies have shown that factors involved in the development of persistent LBP-related disability include psychological, biological, social, and environmental influences [5, 6]. Since disability management in rehabilitation focuses on functioning, the International Classification of Functioning, Disability and Health (ICF) framework is preferred by medical and rehabilitation professionals, as it represents a biopsychosocial framework that provides an overall view of the different aspects of health (biological, individual, and social) [7, 8]. It could serve as the foundational underpinning of a comprehensive framework to better guide the rehabilitation management of LBP.

In order to more effectively manage LBP through rehabilitation approaches, evidence endorses that rehabilitation professionals use classification systems (CS) to help formulate their diagnosis and guide treatments [9]. While CS have improved our understanding of LBP profiles and risk stratification, they have shown limitations. We must recognize that the classification systems currently available CS for the management of LBP 1) mostly focus on addressing deficits related to biological aspects explaining pain and disability and 2) poorly integrates contextual factors driving the experience of pain, such as the person’s environment (social, physical) and inherent personal factors [10]. These aspects can lead to 1) an incomplete clinical profile, 2) inadequate or inappropriate specific relevant interventions (i.e., providing thrust manipulations alone to a patient presenting high levels of cognitive-affective factors) which ultimately lead to modest clinical outcomes [10, 11]. Currently, the use of CS alone can create diagnostic uncertainty which can be define as a perception of lack of knowledge that can change overtime and impedes the clinician’s ability to initiate definitive treatment for a stated problem [12], lead to generic versus personalized care, and put unnecessary stress on already limited resources [10, 11]. Hence, a more comprehensive and broader perspective is needed.

With that in mind, we recently proposed and validated a non-pharmacological management model (The Low Back Pain and Disability Drivers Management (PDDM) model) that encompasses the multidimensional elements included within the ICF framework [13]. Detailed description of the model is presented elsewhere [13]. Our model is distinct from previous research in this area, as it does not propose a new CS. Rather, the PDDM build upon decades of LBP research to provide the first theory-informed guide to improve clinical decision-making processes. It aims to identify the domains influencing pain and disability to create an ICF-based profile or phenotype to guide clinical decisions. Our model is composed of five domains upon which the clinician can base his assessment and orientate treatment allocation and includes: 1) nociceptive pain drivers (i.e., somatic, inflammatory or mixed pain), 2) nervous system dysfunction (NSD) drivers (i.e., sensitization of the peripheral and/or central nervous system), 3) comorbidity drivers (i.e., physical and/or mental health comorbidities), 4) cognitive-emotional drivers (i.e., maladaptive cognitions and/or behaviors) and 5) contextual drivers (i.e., occupational-related and social environmental contextual drivers) [13]. Each domain contains two categories, the first (A) implicates more common and/or modifiable factors, whereas the second (B) involves more complex elements. Patient management should be individualized to the combined contribution of each domain driving the experience of pain and disability. Thus, this profiling will inform and lead the clinician’s treatment approach.

Ultimately, we hypothesize that such a theoretical framework will help rehabilitation clinicians provide more targeted care, optimize treatment outcomes as well as resource utilization in the management of LBP. As our newly developed model has shown sufficient face validity to potentially guide the non-pharmacological management of LBP [14], the next step is to assess its feasibility with clinicians and a sample of patients presenting with non-specific LBP. Although we’ve previously laid the conceptual components of the model and identified the optimal tools to assess the elements included within each domain of the model [14], we have yet to gather data in regard to its feasibility (acceptance, barriers and facilitators to the clinical use of the model) and preliminary effects on clinical outcomes. Hence, prior to implementation and assessment of its effectiveness through a multisite randomized control trial (RCT), we need to gather pilot data regarding these important aspects.

**Objectives**

The general objective of this project is to assess the feasibility of conducting a complete RCT to evaluate the impact of the PDDM model on improving the management of non-specific LBP. The specific objectives are:

- To evaluate the feasibility of the PDDM to guide assessment and treatment;
- To document the clinicians’ acceptability and patient satisfaction of its use in clinical settings;
- To explore the model’s short-term effect on patient’s clinical outcomes (gather preliminary evidence of change in levels of pain and disability and quality of life).

**Methods**

**Design**

A prospective single arm design will be carried out to test the clinicians’ acceptability and the feasibility of the intervention for people with non-specific LBP as well as to gather preliminary data on its effectiveness through quantitative and qualitative methods. The CONSORT statement extension for feasibility trials [15] and the SPIRIT statement list [16] guided the development of this feasibility study protocol.

**Study setting**

Participants (clinicians and patients) will be recruited from two different orthopedic physiotherapy clinics: the orthopedic physiotherapy outpatient clinic of the Centre Hospitalier Universitaire de Sherbrooke (CHUS) and private physiotherapy clinics from the network of clinics of *PhysioExtra* in the greater region of Montreal, Quebec. These clinical settings have already expressed interests in participating and we’ve already established collaborations with the physiotherapists (PT) from the two sites from past research projects. Also, they have access to a large population of patients suffering from musculoskeletal disorders (MSD), such as non-specific LBP. Moreover these 2 settings representing both the private and public sectors of the healthcare system in Quebec will contribute to the external validity of the study.

**Participants**

To be included, PTs will have to 1) be working with a population suffering from MSD such as LBP and have a valid license to practice physiotherapy in the province of Quebec, 2) agree to participate to the one-day training workshop (intervention), 3) assess and initiate treatment of their patients presenting with non-specific LBP guided by our newly developed model. Patients presenting with non-specific LBP according to the assessment conducted by the PT will be eligible to participate in the study and will have to agree to provide patient related-outcomes obtained following their assessment/treatment in physiotherapy.

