**Recruitment**

A convenience sampling method will be used to recruit the clinicians. PTs from the two sites that express interest in participating in the study will be enrolled if they meet the inclusion criteria. An email containing all the relevant and necessary details to participate in the study including the participant’s (PTs) implication and the research team coordinates will be sent to all the clinicians from both sites (see [Appendix A](#_Annex_A:_invitation)). Patients participating in the study will be recruited based on the participating clinicians’ caseload. Each PT will have to recruit participants (new patients) by explaining in detail the purposes, process and implications of participating in the study. A formal consent form with all the aforementioned details will be provided by the PT to the patient. As this is a feasibility trial, no formal sample size calculation was conducted [17]. Instead, we aim to recruit between 10-15 PTs in order to effectively measure the feasibility of implementation of the intervention in a 3-4 months timeframe. We aim to have each PT provide complete data for at least five of their patients with non-specific LBP for an expected total of 50-75 patients.

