**Feasibility outcomes**

The feasibility outcomes include:

1. Recruitment rate: % of eligible clinicians (T1) and patients who enrolled in the study (T2)
2. Retention rate: % of contacted clinicians and patients accepting to participate and report data (T3);

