**Ethical considerations**

Informed consent from all participants to participate in this study will be obtained. For the PTs, their consent will be obtained via a consent form handed to them at the beginning of the training workshop. Since the patients are already seeking and/or receiving healthcare services, only their consent to fill out questionnaire for the purpose of the study will be obtained by the PTs themselves via a second consent form with detailed information concerning the study process and their implication. In fact, the care received by the patients in this study is in the same continuum of standard care. They will be advised that all collected data would be kept confidential and anonymized by the use of alphanumeric coding only known to the researchers. Patients will receive a 20 $ Amazon electronic gift card to compensate for the time necessary to complete all the questionnaires at the time of the final visit (T3).

All electronic identifiable information will be held on a secure, password-protected database, accessible only to the members of the research team. Paper forms with identifiable information will be held in secure, locked filing cabinets within a restricted area. All paper and electronic data will be retained for at least 5 years after completion of the trial. There is no additional risk or inconvenient for the PT or the patient related to their participation in the study.

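### Read literally, the physiotherapist recruitment rate is close to 100% by construction, because agreeing to the workshop is part of eligibility; its denominator needs redefining

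*Protocol*

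**What the plan says.** Three parts of the protocol bear on the PT rate.

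- **Participants.** There are three conditions for a PT to be included. The first is a Quebec licence and a caseload of musculoskeletal disorders. The second and third are to "agree to participate to the one-day training workshop (intervention), 3) assess and initiate treatment of their patients presenting with non-specific LBP", with the PDDM model as the guide.
- **Recruitment.** An e-mail "will be sent to all the clinicians from both sites", and "PTs from the two sites that express interest in participating in the study will be enrolled if they meet the inclusion criteria".
- **Feasibility outcomes.** Item 1 is "Recruitment rate: % of eligible clinicians (T1) and patients who enrolled in the study (T2"). Item 2 is "Retention rate: % of contacted clinicians and patients accepting to participate and report data (T3").

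The Outcomes section places T1 after the workshop. Ethical considerations says that PTs sign their consent form as the workshop begins. Outcomes also lists the willingness of individuals to take part among the things that feasibility covers.

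For patients, the treating PT decides by assessment who has non-specific low back pain, recruits new patients from their own caseload, and provides the consent form. The aim is complete data on at least five patients per PT.

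**The concern.** Willingness to take part is one of the things this study sets out to measure, and criterion 2 turns it into an entry condition. If the same list defines who is eligible, PTs who say no to the workshop are removed from the denominator before the rate is calculated. What is left is a comparison of PTs who agreed with PTs who agreed.

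The general objective is to judge whether a full randomised trial can be run. A recruitment rate that cannot come out low gives the planners of that trial no information on how many PTs or clinics they must approach. The protocol lists only two feasibility outcomes, and this is the first. Denominators that are not recorded while recruitment is under way are hard to rebuild later. Eligibility and the definition of a primary outcome are fixed in this protocol, so this is not a detail left for an analysis plan.

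**Working it through.** **Inputs from the protocol.** Target of 10-15 PTs; at least 5 patients per PT; expected total of 50-75 patients; no formal sample size calculation.

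**Inputs assumed.** The protocol does not give the number of PTs e-mailed, M; I take 20 to 60. For patients, I take the share of eligible patients approached, a, as 25-100%, and consent among those approached, c, as 80% for illustration.

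**Step 1: the plan's own figure.** 10 × 5 = 50 and 15 × 5 = 75. The expected patient total reproduces.

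**Step 2: PT rate on the literal reading.** Rate = enrolled / PTs meeting all three criteria. PTs who agree to the workshop and meet the rest are enrolled, so the rate is 10/10 = 100% or 15/15 = 100%. It drops only if a PT agrees and then withdraws before enrolment. One such PT gives 10/11 = 91% or 15/16 = 94%.

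**Step 3: PT rate with all e-mailed PTs as denominator.** Rate = enrolled / M, taking all M to meet criterion 1.

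| PTs e-mailed (assumed) | 10 enrolled | 15 enrolled |
| --- | --- | --- |
| 20 | 50% | 75% |
| 30 | 33% | 50% |
| 40 | 25% | 38% |
| 60 | 17% | 25% |

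Uptake therefore runs from 10/60 = 17% to 15/20 = 75%. The gap to the literal rate is 100 − 75 = 25 to 100 − 17 = 83 percentage points.

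**Step 4: does item 2 make up for it?** Item 2 divides by those contacted, so it does react to low uptake. Suppose 60 PTs are e-mailed. If 15 enrol and 10 report data at T3, item 2 is 10/60 = 17%. If 10 enrol and all 10 report, it is again 10/60 = 17%. Uptake is 25% in the first case and 17% in the second; retention among enrolled PTs is 10/15 = 67% in the first and 10/10 = 100% in the second. Item 2 cannot separate the two.

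**Step 5: patients.** Agreement stands beside patient eligibility and is not part of it, so the tautology does not carry over. The stated rate is consented / eligible = a × c. With c = 80%, it is 80% × 25% = 20% up to 80% × 100% = 80%, while consent among those approached stays at 80% throughout. To report the stated rate, someone must count eligible patients who were not approached. The protocol states neither a consecutive approach nor a record of that count.

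**The case against.** The strongest reply is that the Participants section uses the word eligible only for patients; for PTs it says what is needed to be included. Eligible clinicians could then mean licensed PTs with a suitable caseload, with agreement to the workshop being the act of enrolling. On that reading the rate is informative. This stands as a possible intention, but the text does not say so. All three conditions sit in one list, and the Recruitment section enrols interested PTs who meet the inclusion criteria as a whole. Two readings that differ by 25 to 83 points under the assumed range need a sentence to settle them.

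Second, item 2 uses contacted clinicians, and the invitation goes to every clinician at both sites, so poor uptake would not be wholly hidden. This also stands in part. The information is there, but it is labelled retention and combined with data reporting at T3.

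Third, the protocol is open about its sampling ("A convenience sampling method will be used to recruit the clinicians"), the feasibility outcomes are descriptive, and no threshold is tied to the recruitment rate. That limits the harm, since no formal decision is triggered. It does not make the rate measure willingness.

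**Conclusion.** The point holds for PTs on the literal reading: the recruitment rate is about 100% by construction, against 17-75% if 10-15 PTs enrol from an assumed 20-60 e-mailed. The size depends on that assumed range; the direction does not. For patients the conclusion is weaker: the rate is not fixed in advance, but its denominator depends on the treating PT alone.

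Three stronger conclusions that a reader might draw are not supported.

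- *That a trained PT who never uses the model is dropped from the denominator through criterion 3.* PTs consent at the start of the workshop and are counted at T1, before any patient is seen at T2. Such a PT is already enrolled, nothing removes them afterwards, and the feasibility list contains no rate of model use. Criterion 3 can work only as an undertaking at entry.
- *That PTs will hand-pick patients to reach a fixed number.* At least five is a minimum, not a cap, and no text permits picking. The protocol is only silent on how patients are approached, and a log may exist in operational documents that are not shown.
- *That the patient consent is flawed because it is not consent to a trial.* The protocol says openly that "only their consent to fill out questionnaire for the purpose of the study will be obtained by the PTs themselves", in a single-arm study within standard care. It nowhere claims that the patient rate estimates willingness to be randomised.

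**What to change.** 1. **PT recruitment:** define it as PTs who consent divided by all e-mailed PTs who meet criterion 1 (licence and musculoskeletal caseload). Record the number e-mailed at each site.
2. **Criteria 2 and 3:** keep them, but describe them as undertakings given at consent that do not define the denominator.
3. **Retention:** define it as enrolled PTs and patients who report data at T3, divided by those enrolled, with PTs and patients shown separately.
4. **Patients:** ask each PT, after the workshop, to approach consecutive new patients with non-specific low back pain and to keep one line per patient: eligible, approached, consented. Report consented divided by eligible.

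This takes a short edit to Participants, Recruitment and Feasibility outcomes, plus a simple log for each PT. The price is a few minutes of PT time per week and a recruitment figure that will look less favourable. It changes nothing in patient care.

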**Recruitment**

A convenience sampling method will be used to recruit the clinicians. PTs from the two sites that express interest in participating in the study will be enrolled if they meet the inclusion criteria. An email containing all the relevant and necessary details to participate in the study including the participant’s (PTs) implication and the research team coordinates will be sent to all the clinicians from both sites (see [Appendix A](#_Annex_A:_invitation)). Patients participating in the study will be recruited based on the participating clinicians’ caseload. Each PT will have to recruit participants (new patients) by explaining in detail the purposes, process and implications of participating in the study. A formal consent form with all the aforementioned details will be provided by the PT to the patient. As this is a feasibility trial, no formal sample size calculation was conducted [17]. Instead, we aim to recruit between 10-15 PTs in order to effectively measure the feasibility of implementation of the intervention in a 3-4 months timeframe. We aim to have each PT provide complete data for at least five of their patients with non-specific LBP for an expected total of 50-75 patients.

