**Outcomes**

The primary outcomes measures will assess feasibility of implementation, clinician’s acceptability and patient’s satisfaction of the intervention. These outcomes will be measured at T0 (i.e., before the workshop), T1 (i.e., after the workshop), T2 (i.e., at patient’s initial visit/enrollment) and T3 (i.e., after follow-up period) (see Figure 1). Sekhon et al. defined acceptability as a “multi-faceted construct that reflects the extent to which people delivering or receiving a healthcare intervention consider it to be appropriate” [18]. It includes several constructs such as attitude towards the intervention, the intervention’s burden and ethicality for the individual, the intervention coherence, perceived effectiveness and self-efficacy in performing the intervention. Feasibility refers to the assessment of whether or not it will be feasible to conduct an intervention in a particular setting and includes issues such as willingness of individuals to participate in the study, the adherence/compliance of participants to the intervention (ex : response rate to questionnaire, loss to follow up) and whether the intervention can be delivered as intended within the clinical setting [19]. Despite the fact that there is some overlap between these constructs, we decided to use specific data collection procedures for each aspect included in these constructs.

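### The only patient target counts completers with no allowance for loss, and retention, a primary feasibility outcome, is taken over those contacted instead of those enrolled

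*Protocol*

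**What the plan says.** The Recruitment section of the protocol gives the number of clinicians, "we aim to recruit between 10-15 PTs in order to effectively measure the feasibility of implementation of the intervention". The only patient target in the document follows, and asks of every clinician "complete data for at least five of their patients with non-specific LBP for an expected total of 50-75 patients". The section is open about the basis: "As this is a feasibility trial, no formal sample size calculation was conducted". The same section has each PT recruit new patients from their own caseload. Under Participants, the PT's own assessment decides who is eligible.

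The Outcomes section gives these measures primary status: "The primary outcomes measures will assess feasibility of implementation". Among the components of feasibility it names "response rate to questionnaire, loss to follow up". The Feasibility outcomes section lists two measures. The first is recruitment, a percentage of those eligible. The second reads "Retention rate: % of contacted clinicians and patients accepting to participate and report data (T3".

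The protocol gives no planned number enrolled and no allowance for losing patients or PTs. It has no rule on consecutive enrolment, on replacing patients who are lost, or on when a PT stops enrolling. It does not ask for a log of all patients approached and enrolled.

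**The concern.** Three things meet here.

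- **Unit of the target.** The patient number is expressed in completers. How many enrolled patients become completers is one of the things the study sets out to measure, so the target cannot be turned into an enrolment figure without assuming the answer. A reader who takes 50-75 as the number enrolled assumes complete retention.
- **Denominator of retention.** Read literally, the measure is the share of those contacted who both agree to take part and report data at T3. That is a product of uptake and retention. A low value could come from either, and the two call for different remedies in the planned randomised trial. Uptake already has its own measure in the recruitment rate.
- **Who selects.** The people asked to deliver completers also choose whom to approach. Without a consecutive-enrolment or replacement rule, a PT can favour patients likely to finish, or add patients when some drop out. Retention would then look better than an unselected caseload would give.

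At stake is how far the retention figure can be carried into planning the later trial, and whether the stated sample is a realistic expectation.

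**Working it through.** **Inputs.** From Recruitment: 10 to 15 PTs, and at least five patients with full data per PT. The protocol gives no loss rate, so the patient loss d (10%, 20%, 30%) and the PT loss (10%) are assumptions.

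**1. The plan's own figure.** 10 x 5 = 50 and 15 x 5 = 75. The stated range is reproduced exactly, and each unit in it is a patient with complete data.

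**2. Completers and enrolled under assumed patient loss, no PT lost.** Completers from n enrolled = n(1 - d), rounded down. Enrolment needed for n completers = n/(1 - d), rounded up.

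| Patient loss d | Completers if 50 / 75 are enrolled | Enrolment needed for 50 / 75 completers |
| --- | --- | --- |
| 10% | 45 / 67 | 56 / 84 |
| 20% | 40 / 60 | 63 / 94 |
| 30% | 35 / 52 | 72 / 108 |

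If 10% of PTs are lost entirely and 20% of the remaining patients are lost: 50 x 0.9 x 0.8 = 36 and 75 x 0.9 x 0.8 = 54 completers.

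**3. One PT enrolling exactly five.** With independent losses, the chance that all five complete is (1 - d)^5: 0.9^5 = 0.59, 0.8^5 = 0.33, 0.7^5 = 0.17. Most PTs would miss the aim at 20% loss unless they enrolled more than five.

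**4. The retention measure as worded.** Let u be the share of contacted patients who agree and p the share of those enrolled who report at T3. The worded measure equals u x p, and equals p only if everyone contacted agrees. For clinicians the gap could be wide: the invitation email goes to every clinician at both sites, so on a literal reading all of them are in the denominator.

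**5. Would stopping at five completers bias the ratio?** The protocol contains no such rule. This step asks only how much it would matter. If enrolment continues until r completers are reached, the number enrolled N is negative binomial and the expected ratio is E(r/N). For a single PT, r = 5. Pooled over PTs, r = 50 or 75.

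| True retention | One PT, r = 5 | Pooled, r = 50 | Pooled, r = 75 |
| --- | --- | --- | --- |
| 0.60 | 0.645 | 0.605 | 0.603 |
| 0.70 | 0.738 | 0.704 | 0.703 |
| 0.80 | 0.828 | 0.803 | 0.802 |
| 0.90 | 0.915 | 0.902 | 0.901 |

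The pooled ratio is too high by about 0.1 to 0.5 percentage points, which is negligible. The excess of 1.5 to 4.5 points in the r = 5 column arises only if rates are computed PT by PT and averaged, and the protocol describes no such averaging.

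**6. Selection of likely finishers.** Its size cannot be computed from the document. Only the absence of a safeguard can be shown.

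**The case against.** The wording is an aim with a floor. A PT may enrol more than five, so a target in completers does not exclude loss; it is silent on how many to enrol. The Intervention section asks PTs for data on each of their patients, including those discharged early, which is hard to square with leaving some out. The study has one arm and no power claim, and it discloses that no sample size was calculated. If every enrolled patient is recorded, retention can still be estimated properly. All of this stands, and it limits the weight of the point.

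A reader might go further and infer that the sampling rule itself distorts retention. The document does not support that. It states no stop at five, no replacement and no exclusion of non-completers, and step 5 shows that even strict stopping would barely move a pooled ratio. Recording completers only would make retention 100% by construction, but nothing says this will be done. Favouring likely finishers is a possibility the protocol leaves open; it is not something the protocol describes.

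The objection does not remove the missing enrolled number, the mixed denominator, or the lack of any rule on how PTs choose and replace patients.

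**Conclusion.** The point holds at minor severity. The 50-75 figure is a count of completers and equals the number enrolled only with no loss of PTs or patients. If it is read as enrolment, the expected completers fall to 35-52 at 30% patient loss and to 45-67 at 10%, or to 36-54 with 10% PT loss plus 20% patient loss. If it is kept as a completer aim, it implies enrolling 56-84 to 72-108 over the same range of patient loss. These figures rest on assumed loss rates, because the protocol gives none.

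The retention measure, read literally, mixes uptake with retention whatever the loss rate. It is also open to selection by the PTs, of unknown size. Distortion by a stopping rule is not established and would be negligible in the pooled figure.

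**What to change.** - In Recruitment, state the target as patients enrolled, per PT and in total. One workable form is that each PT enrols the first five consecutive eligible new patients who consent. That gives 50-75 enrolled, with no replacement and with enrolment not dependent on completion.
- Give the expected completers beside it as a range under stated assumed loss, using the figures in steps 2 and 3 of the working. If 50-75 completers is to remain the aim, state the larger enrolment it implies, and fix that number per PT in advance.
- Keep a log of all patients approached and all enrolled.
- In Feasibility outcomes, define retention as T3 completers divided by all enrolled, pooled over PTs, and report uptake separately under recruitment. Define clinician retention in the same way.

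The cost is protocol wording and a simple log. With five enrolled per PT no extra patients are needed, but the stated number of complete cases becomes less favourable. Keeping 50-75 completers instead means more patients to enrol in the same three to four months.
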